The overall aim and primary objective of the RESET-psychotherapy (REStoring mood after Early life Trauma) study is to investigate whether TFT as an adjunctive to treatment as usual (TAU) (experimental condition) leads to more reduction of depressive symptoms at post-treatment when compared to TAU only (control condition) in MDD patients with CT. Secondary objectives are: 1) to determine whether patients who receive adjunctive TFT show more depressive symptom reduction during treatment and at 6-month follow-up than patients who only receive TAU, 2) to examine whether patients in the experimental condition show more improvement in other clinical outcomes in comparison to patients in the control condition (i.e. MDD remission rate, anxiety symptom severity, insomnia, subjective stress and overall functioning and disability), 3) to examine potential mediators (e.g. social support and stressful life events) and moderators (e.g. comorbid PTSD / acute stress disorder (ASD), timing/duration/context of CT, resilience, personality and coping) of the hypothesized beneficial effect of TFT, and 4) to understand neurobiological mechanisms of the expected clinical improvement following TFT.

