### Sample size

Based on earlier results of an add-on TFT on depressive symptoms [55, 56] we estimate to detect a medium-sized between-group effect size (i.e., Cohen’s *d* = 0.50) on the primary outcome measure (depression symptom severity at post-treatment). Based on this assumption, a power of 0.8 (80%) and a two-tailed significance level of p < 0.05, the recruitment of 63 participants per treatment group is required. Considering a conservative drop-out estimate of around 20%, *n* = 79 patients per treatment group are needed, resulting in a total sample size of *n* = 158. As described by Thirion et al. (2007), fMRI analyses require a minimum of 20 participants per group for sufficient reliability [57]. However, to increase power, we strive to recruit more participants for the fMRI sub-study, aiming at a total sample of *n* = 60 (30 participants per treatment group).

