#### Stress-related biomarkers

##### Hair cortisol

At baseline (T0) and post-treatment (T2), hair samples closest to the scalp are collected. Hair cortisol has shown to be a validated measure and stable retrospective marker of long-term systemic cortisol levels over weeks to several months, reflecting more chronic cortisol exposure [85]. At both assessments, a short self-composed questionnaire about the use of hair treatments or products is assessed.

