##### Epigenetic and inflammatory markers

At baseline (T0) and post-treatment (T2), 3 tubes of blood (16 ml) are drawn in all consenting participants to perform future analyses on epigenetic and inflammatory markers underlying the effects of TFT. The inflammatory markers C-reactive protein (CRP), Tumor Necrosis Factor-alpha (TNF-α) and Interleukin-6 (IL-6) will be examined. The DNA that will be extracted from the blood will be used for future exploratory epigenetic research. Epigenetic changes will be analyzed using microarrays, rather than specific genes.

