### Statistical analysis plan

Analyses will be conducted using an intention-to-treat (ITT) approach, including all participants originally allocated to one of the treatment conditions. To estimate the intervention effect across time, linear mixed models (LMM) will be used for both primary and secondary continuous outcomes, with outcome score at different time-points as the dependent variable and time point indicators and treatment-by-time point indicator interaction terms as independent variables. For dichotomous outcomes, generalized estimating equation (GEE) will be used in order to favor population averaged above subject specific results. The significance threshold will be set at alpha = 0.05 and treatment effects will be evaluated in terms of Cohen’s *d*. Since missing data will concern the missing data from patients dropping out of the study, analyzing all observed outcome data using LMMs and GEE is appropriate when data are missing at random [88, 89]. Per-protocol (PP) analyses will be performed in which participants in the control group will be compared to participants of the experimental group who adhered to the study protocol (i.e. followed at least 75% of the minimal amount of 6 TFT sessions). No interim analyses are planned. Stress-related factors will be examined as potential determinants of the treatment effect by studying moderation and mediation (secondary analyses). When concerning moderators, the LMMs and GEE will be augmented by incorporating the corresponding moderator and treatment-by-moderator interaction term. When concerning possible underlying mechanisms using mediation analysis, hypotheses will be tested with the analytic steps outlined by Baron and Kenny, using multiple regression analyses and Sobel’s test to evaluate if the indirect effect of the independent variable on the dependent variable via the mediating variable is significant [90]. Data from the (f)MRI sub-sample will be pre-processed and analyzed using FSL (FMRIB Software Library). To estimate the intervention effect across time, LMMs will be used with structural integrity and resting-state network functionality as dependent variables/outcome measures and time point indicators and treatment-by-time point indicator interaction terms as independent variables.

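### Mediation is to be tested with Baron-Kenny steps and Sobel's test, which lose power at this sample size; an interval for the indirect effect avoids this at almost no cost

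*Protocol article*

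**What the plan says.** The Statistical analysis plan section of the protocol article names the method for underlying mechanisms: "hypotheses will be tested with the analytic steps outlined by Baron and Kenny, using multiple regression analyses and Sobel’s test". It places this work among the secondary analyses ("by studying moderation and mediation (secondary analyses") and sets one threshold: "The significance threshold will be set at alpha = 0.05".

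The secondary objectives at the end of the Background include "to examine potential mediators (e.g. social support and stressful life events"; both are given as examples. A separate objective concerns neurobiological mechanisms. Table 1 schedules social support and stressful life events at T0, T1, T2 and T3. Hair and blood have a single post-baseline value: "At baseline (T0) and post-treatment (T2), hair samples closest to the scalp are collected", and "At baseline (T0) and post-treatment (T2), 3 tubes of blood (16 ml) are drawn in all consenting participants". The fMRI scans follow the same two-visit schedule. The primary outcome, IDS-SR, is taken at T2.

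The only power calculation is for the primary outcome ("we estimate to detect a medium-sized between-group effect size", d = 0.50, with "a power of 0.8 (80%) and a two-tailed significance level of p < 0.05"). No path sizes or power are given for mediation.

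**The concern.** The method is stated, so this is a choice already made and not a detail left open. It has two weaknesses.

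- **Sobel's test.** It divides the product a × b by a delta-method standard error and refers the ratio to the normal distribution. In samples of this size the product is skewed unless both paths are strong, and the test rejects too seldom.
- **The causal steps.** In their classical form they first require a significant total effect. That makes the mediation result depend on a test that fails in about one trial in five even when the planning assumption is true.

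At stake is the mediation part of the secondary objectives. A real mediator with small-to-medium paths could be missed because of the test used. A second, smaller matter is order in time: for markers first re-measured at T2, an analysis against the T2 depression score cannot show which changed first.

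**Working it through.** **1. The plan's own figure.** Two-sided alpha 0.05, power 0.80, d = 0.50:

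n per arm = 2 × (1.960 + 0.842)² / 0.50² = 2 × 7.85 / 0.25 = 62.8, so 63. With 20% dropout: 63 / 0.80 = 78.75, so 79 per arm and 158 in total. The figure reproduces. Power at 63 per arm is 80.1% by the normal formula and 79.5% by the t-test. Evaluable total: 2 × 63 = 126.

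**2. Why Sobel loses power.** Let X be the arm (1:1), M = aX + e, and Y = c'X + bM + e, with within-arm SD 1 for M and Y and total effect c' + ab = 0.50. Take a = 0.5, b = 0.3, so c' = 0.50 − 0.15 = 0.35.

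- SE(a) ≈ √(4/126) = 0.178, so z_a = 0.5/0.178 = 2.81.
- SE(b) ≈ √((1 − 0.3²)/126) = 0.085, so z_b = 0.3/0.085 = 3.53.
- Sobel z = 1/√(1/z_a² + 1/z_b²) = 1/√(0.127 + 0.080) = 2.20.

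Both paths are well past 1.96 at their true values, yet the Sobel ratio only just is. It is always smaller than the weaker of the two path statistics. With equal paths, each needs 1.96 × √2 = 2.77 before Sobel reaches 1.96.

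**3. Simulated power, N = 126.** The path sizes are assumptions. Steps means total effect, a and b each p < 0.05, followed by Sobel.

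| a | b | Sobel | Steps + Sobel | Bootstrap or Monte Carlo interval |
|---|---|---|---|---|
| 0.3 | 0.3 | about 20% | about 18% | 35-38% |
| 0.5 | 0.3 | 52-57% | 43-49% | 71-73% |
| 0.5 | 0.5 | 76-79% | 58-69% | 80-82% |
| 0.8 | 0.5 | 99% | 79% | over 99% |

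Ranges span repeated runs. A run of 1,000 trials has a standard error of up to √(0.25/1,000) = 1.6 points. The low end for the steps at a = b = 0.5 comes mainly from setting the residual SD of Y to 1. The total effect is then 0.50/√(1 + 0.5²) = 0.447 within-arm SDs, so the first step passes less often. No baseline covariates were included.

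**4. The cap.** In the last row the mediator is found almost always by Sobel alone or by the interval, but in 79% of trials once the total effect must be significant. That is the trial's power for the total effect.

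**5. Under no mediation.** With one path zero and the other clearly non-zero, Sobel rejects in about 1% to 3.6% of trials, and the interval in about 4% to 6%. With both paths zero, both reject almost never (about 0% and 0.3%).

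**6. The fMRI subsample.** N = 60 as planned; N = 48 if 20% dropout is assumed here too (60 × 0.80).

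| N | a | b | Sobel | Steps + Sobel | Bootstrap |
|---|---|---|---|---|---|
| 60 | 0.5 | 0.3 | 13% | 8% | 30% |
| 60 | 0.5 | 0.5 | 37% | 25% | 50% |
| 48 | 0.5 | 0.3 | 8% | 4% | 21% |
| 48 | 0.5 | 0.5 | 24% | 15% | 39% |

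At N = 60, a = 0.5, b = 0.3, the gap from 8% to 80% is 72 points. Changing the test recovers 22; the other 50 are sample size.

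**The case against.** The size of the loss rests on path sizes that the article does not state. Sobel alone gives up only about 3 or 4 points when a = b = 0.5. A reader might infer that the mediation analyses are badly underpowered and will probably give false negatives. The document does not support that as a general statement; it holds only for small-to-medium paths. The article also does not spell out that a significant total effect is required, so the cap is conditional on the classical first step. A conservative test makes a false claim of mediation less likely. All of this stands.

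A reader might also infer that the mediators are measured only at the outcome visit. That is wrong for the two that the article names, which have T1 values before T2. Hair, blood and MRI measures are not listed as mediators; they serve the mechanism objective, and structural and resting-state MRI measures are modelled as outcomes. The wording about underlying mechanisms could cover them, but the article nowhere says that a T2 marker will be set against T2 IDS-SR. Hair cortisol is also described as retrospective over weeks to months, so a T2 sample partly reflects earlier exposure.

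It is tempting to add that multiple regression discards incomplete cases. The article does not say how missing data are handled for mediation, so that is not shown.

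**Conclusion.** The point holds as a better method available at almost no cost. Baron-Kenny steps with Sobel's test are conservative at about 126 evaluable participants. Against an interval for the indirect effect, Sobel alone loses roughly 15 to 20 points of power when b = 0.3 and a is 0.3 to 0.5, and little when b is about 0.5. If the total-effect step is applied, power stays at or below about 80% whatever the mediator's strength. These figures assume a total effect of 0.50, normal errors, no baseline adjustment and the stated range of paths.

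For the fMRI subsample the change helps but cannot rescue mediation. For hair, blood and MRI, the order of marker and T2 mood cannot be shown from the schedule, which limits how any such result should be worded. The analyses are secondary and the primary conclusion does not depend on them.

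**What to change.** Replace the mediation sentence with:

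> The indirect effect (a × b) is estimated with adjustment for the T0 mediator and T0 IDS-SR and judged by a 95% percentile-bootstrap or Monte Carlo interval; a significant total effect is not required.

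Add two statements on timing:

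- For social support and stressful life events, the T1 value is the mediator of T2 IDS-SR. The six-month recall of the life-events list reaches back before randomisation, so its T1 score is not purely post-randomisation; say so when reporting.
- Any mediation analysis of hair, blood or MRI markers on T2 IDS-SR is reported as associational.

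Pairing T2 markers with T3 IDS-SR is not a clean way round the timing limit. Adjusting for T2 IDS-SR would condition on a post-randomisation variable, the question would become change after T2, and the instruction to TAU therapists not to give TFT for childhood trauma ends at T2.

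The cost is a change of wording and a little computation. No visit or measurement is added.

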### Data management and quality assurance

After inclusion, participants receive a unique, coded participant number that contains no identifiable information. All data are collected digitally whenever possible, using Castor EDC, and de-identified using this coded number. An administrative database will be used to ensure timely assessments. Participants who discontinue their treatment or deviate from the study protocol are encouraged to continue the research assessments to minimize loss of follow-up data. Once collected, de-identified data are backed up periodically and centrally stored and managed by the data management team of the Amsterdam UMC. Data will be stored 15 years upon completion of the study and will be destroyed after this time. The video recordings and/or audio recordings of the TFT sessions are securely stored at the digital network of the mental health organization where the participant receives treatment. The recordings will be destroyed one year upon completion of the study. The study is guided by the study team, which also acts as the steering committee. The study team consists of the PI, co-principal investigators, junior researchers, RA’s, and site investigators (Additional file 1: Appendix C). All amendments to the study protocol will be notified to the accredited MREC. A meta-analysis shows that a small percentage of patients deteriorate from psychotherapy [91]. However, previous studies on (additional) trauma treatments for depression reported no adverse side effects of treatment [48, 56, 92]. In our study, the well-being of study participants and study procedures will be properly monitored. Accordingly, an independent clinical research associate (CRA) of the Clinical Monitoring Center (CMC) of the Amsterdam UMC carries out monitoring visits during and after the study based on a study-specific monitoring plan. Therefore, extra monitoring is not considered necessary and a data monitoring committee (DMC) is not installed.

### Adverse event reporting

The current study is associated with a moderate risk as patients with moderate to severe MDD and CT can be seen as a vulnerable patient group. Solicited and spontaneously reported adverse events (AEs) are assessed in a structured manner during the study measurements. All SAEs that are associated with mental health excesses or death are reported to the accredited MREC according to its requirements after obtaining knowledge of the events. All (S)AEs are followed up until they have abated or until a stable situation has been reached.

### Data dissemination

The study findings will be published in scientific, peer-reviewed journals and disseminated through presentations at scientific conferences. Results will be communicated to participants through the website of the Dutch Psychiatry Association, the Dutch Knowledge center for Anxiety and Depression (NedKAD), as well as the Dutch Depression Association and Dutch Patient Federation MIND. Findings will also be communicated to appropriate national and international media for a lay audience.

### Trial status

The RESET-psychotherapy study is pre-registered at ClinicalTrials.gov (registered at 08–12-2021, identification number: NCT05149352). Recruitment started in November 2021 and is ongoing. Recruitment of the fMRI sub-study is expected to start in September 2022.

## Discussion

There is increasing evidence that patients with MDD and CT represent a neurobiologically and clinically distinct MDD subtype. Compared to those without CT, depressed patient with MDD show aberrant cortisol levels [18, 19] and elevated inflammation [20, 21]). Also, previous studies have found that the experience of CT influences brain structure, function and connectivity [23], with different neurodevelopmental effects observed for individuals that have been exposed to threat (i.e. reduced amygdala, medial prefrontal cortex (mPFC), and hippocampal volume and heightened amygdala activation to threat) compared to individuals that have been exposed to deprivation (i.e. reduced volume and altered function in frontoparietal regions) [93]. When it comes to the clinical presentation, MDD patients with a history of CT have an earlier onset and unfavorable disease course compared to their non-maltreated counterparts [9, 26–29]. Given the high prevalence of CT in adult MDD and the finding that patients with CT report higher depression symptom severity after depression treatment [16], there is a large and unmet need for novel treatment strategies to alleviate depressive symptoms in this patient group. The RESET-psychotherapy study is the first RCT that investigates the efficacy of TFT, as an adjunctive to TAU, in reducing depression symptom severity in a large sample of adult MDD patients with a history of CT. In addition, this study aims to provide information for whom and under which conditions this adjunct TFT would be most efficacious, by providing insight into (neurobiological) mechanisms underlying the TFT treatment effect. The RESET-psychotherapy study has several strengths. First, besides focusing on reducing depression symptom severity, other comorbid symptoms and problems are examined as secondary treatment outcomes. Second, a broad range of potential effect modifiers is included to determine the efficacy of adjunctive TFT and to gain more insight into the underling working mechanisms. Finally, the study is considered to have good methodological quality, with the use of both self-report questionnaires and semi-structured interviews, treatment integrity assessments, and professional trainings and supervisions by experts in the field of EMDR and ImRs. A limitation of the study is that participants in the experimental condition receive more treatment sessions than patients in the control condition. Therefore, a possible attention effect should be considered when interpreting study results. A second limitation is that some exclusion criteria (i.e. the presence of BPD, a psychotic disorder, or a bipolar disorder) are assessed using a telephone screening in which patients are asked if they have ever been diagnosed with these mental disorders. This form of assessment is not as reliable as using a diagnostic interview to assess the presence of these diagnoses. However, in all participating centers, study participants are diagnosed by an experienced clinical psychologist or psychiatrists and the presence of a current comorbid PTSD or ASD is checked/identified during the baseline assessment by using the PTSD and ASD section of the MINI-S interview. In the current study, patients with BPD are excluded as depressive patients with BPD represent a different patient population, warranting other TAU modalities (e.g. dialectical behavior therapy or mentalization-based treatment). However, as BPD patients often have a history of CT [94], it is probable that a part of the patients who meet the study inclusion criteria cannot not be included based on this exclusion criterion. Lastly, CT is assessed by the sole use of a retrospective self-report measure (CTQ-SF). Meta-analytic findings have shown poor agreement between retrospective reports and prospective measures of CT, suggesting that the underlying mechanisms of psychopathology in those who retrospectively report CT may be different from those for which CT is determined through prospective measures [95]. Thus, caution should be made when generalizing study findings. It is expected that TFT will be a safe and rational strategy to reduce depressive symptoms in MDD patients with CT. If adjunctive TFT would be more efficacious than TAU only, this would be a novel hypothesis-driven treatment strategy for an important MDD subtype and pave the way for a more personalized and targeted MDD treatment.

## Data Availability

Individual participant-level data (IPD) that underlie the study results will be shared in scientific, peer-reviewed journals after de-identification (text, tables, figures and appendices). Trial data can be requested by submitting an analysis plan and data request to the principle investigator (PI) [name] (see Additional file 1: Appendix D for contact information) who will check on the adequacy and relevance of the proposed data analyses. After approval, the data management team of the Amsterdam UMC, location VUmc will provide permission and access to use the data upon reasonable request.

## Abbreviations

AE: Adverse event
ASD: Acute Stress Disorder
AUDIT: Alcohol Use Disorders Identification Test
BAI: Beck Anxiety Inventory
BMI: Body Mass Index
BOLD contrast: Blood Oxygenation Level-Dependent contrast
BPD: Borderline Personality Disorder
CBT: Cognitive Behavioral Therapy
CD-RISC: Connor-Davidson Resilience Scale
CMC: Clinical Monitoring Center
CRA: Clinical Research Associate
CRP: C-Reactive Protein
C-SSRS: Columbia-Suicide Severity Rating Scale
CT: Childhood Trauma
CTQ-SF: Childhood Trauma Questionnaire—Short Form
DSM-5: Fifth edition of the Diagnostic and Statistical Manual of Mental Disorders
DTI: Diffusion Tensor Imaging
EHR: Electronic Health Record
EMDR: Eye Movement Desensitization and Reprocessing
EPIs: Echo Planar Images
fMRI: Functional Magnetic Resonance Imaging
FSL: FMRIB Software Library
IC: Informed Consent
IDS-SR: Inventory of Depressive Symptomatology—Self Rated
IL-6: Interleukin-6
ImRs: Imagery Rescripting
IPAQ: International Physical Activity Questionnaire
IPT: Interpersonal Therapy
ISI: Insomnia Severity Scale
LMM: Linear Mixed Models
LTE: List of Threatening Experiences
MACE: Maltreatment and Abuse Chronology of Exposure
MDD: Major Depressive Disorder
MINI-S: Mini International Neuropsychiatric Interview – Simplified
mPFC: Medial Prefrontal Cortex
MREC: Medical Research Ethical Committee
NEO-FFI: Neuroticism–Extroversion–Openness Five Factor Inventory
PE: Prolonged Exposure
PI: Principal Investigator
PSS: Perceived Stress Scale
PTSD: Posttraumatic Stress Disorder
RA: Research Assistant
RESET: REStoring mood after Early life Trauma
SAE: Serious Adverse Event
SSL-I: Social Support List –Interaction
SUD: Subjective Unit of Distress
TAU: Treatment As Usual
TFT: Trauma-Focused Therapy
TNF-α: Tumor Necrosis Factor-alpha
UMC: University Medical Centers
VCVGZ: Vereniging tot Christelijke Verzorging van Geestes- en Zenuwzieken
VUmc: VU University Medical Center
WHODAS: WHO Disability Schedule
WMO: Medical Research Involving Human Subjects Act
